CLBP information	✓	✓	✓	✓	✓				
Diagnosis	✓								
Lumbar imaging	✓								
Informed Consent	✓								
Acupuncture rationale	✓								
Acupuncture details	✓	✓	✓	✓	✓				
Acupuncture regimen	✓								
Combined therapy	✓	✓	✓	✓	✓				
Numerical Rating scale (NRS)	✓				✓	✓	✓	✓	
Oswestry Disability Index (ODI)	✓				✓	✓	✓	✓	
Adverse event	✓	✓	✓	✓	✓	✓	✓	✓	
Disease status						✓	✓	✓	✓

^a^The number of acupuncture treatments shall be no less than three times, ^b^No less than three follow-up visits

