#### Analytic approach

Data with poor compliance, non-compliance with the study program or missing important information are not included in the analysis. Data processing and statistical analysis will use SPSS version 24 (IBM Corp., Armonk, NY, USA) and SAS Version 9.4 (SAS Institute Inc., NC 27513–2414, USA).

We will select 1-week,4-week,12-week, assessments respectively at evaluation time point on the ODI and NRS index. Firstly, baseline characteristics comparability needs to be assessed between the propensity-matched groups. Model adjustment suggested by Rosenbaum and Rubin will be adopted to conquer residual covariance imbalances [42]. Secondly, multivariate linear regression models will be employed to adjust the propensity score and baseline characteristics. Once matched, change in ODI and NRS between-group at different observation points will be calculated by paired t-test. Thirdly, logistic regression models will be used to evaluate the magnitude of impacts contributed by baseline factors on acupuncture effectiveness for CLBP patients. Descriptive analysis will be used for variables such as the recruited research center,s basic characteristics of doctors and patients, initial diagnosis and intervention details. Quantitative data (Height, Weight, NRS, ODI, etc.) will be described by mean, standard deviation, median, maximum and minimum values. The enumeration data (Acupuncture style, Acupoint selection principle, Operation of acupoints, Effective rate etc.) and ranked data (Educational background, Physician title) will be described by numbers, percentages, rate and constituent ratio. If necessary, parametric methods or alternate nonparametric methods will be selected appropriately.

We will adopt the propensity score matching of patients at 1:1 to imitate an RCT. Baseline confounder will be equilibrated and matched on variables such as demographic data, medical history, duration, intensity, back function. The comparative analysis will be conducted after the baseline unevenness adjustment. Propensity score will match comparison group, such as Traditional Chinese acupuncture style vs Microacupuncture style (Scalp acupuncture, Ear acupuncture, Wrist and ankle acupuncture, Eye acupuncture, Umbilical acupuncture, Abdomen acupuncture), Local acupoint selection vs Non-local acupoint selection and Single Acupuncture vs Combined therapy etc.

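### The matched comparison of NRS and ODI is a paired t-test on raw change that does not use the baseline score, and the plan does not say whether this or the planned regression gives the between-group result

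*Protocol article*

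**What the plan says.** The Analytic approach section of the protocol article sets out 1:1 propensity score matching ("We will adopt the propensity score matching of patients at 1:1 to imitate an RCT") for three named regimen contrasts: traditional versus micro-acupuncture style, local versus non-local point selection, and acupuncture alone versus combined therapy. Patients are to be "matched on variables such as demographic data, medical history, duration, intensity, back function".

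Four statements in that section bear on the analysis after matching:

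- Baseline comparability of the matched groups is assessed first, and "Model adjustment suggested by Rosenbaum and Rubin will be adopted to conquer residual covariance imbalances".
- As a second step, "multivariate linear regression models will be employed to adjust the propensity score and baseline characteristics".
- Directly after that: "Once matched, change in ODI and NRS between-group at different observation points will be calculated by paired t-test".
- Later: "The comparative analysis will be conducted after the baseline unevenness adjustment".

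Table 2 (Data elements and collection methods) shows NRS and ODI recorded at the first visit, at the last visit and during follow-up. The baseline value of each scale is therefore available for every analysis of change.

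**The concern.** The only sentence that says how the between-group change in the two scales is calculated names a paired t-test, and that test cannot carry a covariate. Change is negatively related to baseline: a patient who starts with more pain is expected to fall further under either regimen. Leaving baseline out therefore leaves avoidable noise in the within-pair difference. If matching leaves one group higher on average at baseline, part of that difference enters the contrast.

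The regression in the preceding sentence could deal with both problems. However, the text neither makes it the source of the regimen difference nor lists the baseline score among its covariates. Two analyses of the same contrast are thus named with no stated order. The contrasts concern the primary outcomes and feed the aim, stated in the abstract, of identifying a preferred regimen.

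**Working it through.** **Inputs from the document.** The outcome is change in NRS and ODI, analysed at 1, 4 and 12 weeks. Matching is 1:1. Both scales are measured at the first visit. Pain intensity and back function are among the matching variables. The article gives no SD, baseline/follow-up correlation, target difference or significance level for these contrasts, so there is no planned figure to reproduce.

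**Assumptions.** Equal SD s at baseline and follow-up; baseline/follow-up correlation rho; correlation c between the baselines of two patients in a pair; two-sided 5% level.

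**Precision.** Write follow-up as rho × baseline plus an independent error with variance s²(1 - rho²). The within-pair difference in change then has

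- variance unadjusted: 2s²(1 - c)(1 - rho)² + 2s²(1 - rho²);
- variance after adjusting for the baseline difference: 2s²(1 - rho²);
- ratio: 1 + (1 - c)(1 - rho)/(1 + rho).

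Extra pairs needed by the t-test on change:

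| | rho = 0.3 | rho = 0.5 | rho = 0.7 |
|---|---|---|---|
| c = 0 | 54% | 33% | 18% |
| c = 0.5 | 27% | 17% | 9% |
| c = 0.8 | 11% | 7% | 4% |

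For example, at rho = 0.5 and c = 0.5 the ratio is 1 + 0.5 × 0.5/1.5 = 1.167.

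**What this means for power.** Assume 200 matched pairs (a regimen used by 10% of 2000 patients), s = 2 NRS points, a true difference of 0.5 points and rho = 0.5.

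- Adjusted: variance 2 × 4 × 0.75 = 6; SE = √(6/200) = 0.173; power = Φ(0.5/0.173 - 1.96) = 82%.
- t-test on change, c = 0: variance 2 + 6 = 8; SE = 0.200; power = Φ(2.50 - 1.96) = 70.5%.
- t-test on change, c = 0.5: variance 1 + 6 = 7; SE = 0.187; power = Φ(2.67 - 1.96) = 76%.
- t-test on change, c = 0.8: variance 0.4 + 6 = 6.4; SE = 0.179; power = Φ(2.80 - 1.96) = 80%.

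With 1000 pairs, both methods have power near 100% for the same difference.

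**Bias.** If the matched groups differ in mean baseline by d, the expected contrast in change shifts by -(1 - rho)d when the baseline-adjusted model is correct. At rho = 0.5, a mean imbalance of 0.4 NRS points (0.2 SD at s = 2) gives 0.5 × 0.4 = 0.2 points. If d = 0 there is no shift, however far apart individual pairs are.

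**Simulation check** (500 pairs, rho = 0.5, 4000 replicates; SD units):

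| Setting | t-test on change | Baseline-adjusted |
|---|---|---|
| No effect, d = 0, c = 0: type I error | 5.4% | 5.6% |
| No effect, d = 0.1, c = 0: type I error | 12.3% | 5.2% |
| No effect, d = 0.1, c = 0.5: type I error | 12.7% | 5.0% |
| Effect 0.15, d = 0, c = 0: power | 65% | 78% |
| Effect 0.15, d = 0, c = 0.5: power | 71% | 78% |

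**The case against.** The strongest reply is that baseline is not ignored. The plan matches on pain intensity and back function, checks comparability, provides for model adjustment of residual imbalance, places the comparison after that adjustment, and plans a regression on baseline characteristics. This stands. It would be wrong to say that every leftover imbalance must reach the reported result.

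A reader might infer that the paired t-test is the analysis that ranks the regimens. The article does not say so. It gives no order between the t-test and the regression, and a condensed article may leave that order to an analysis plan that is not shown. Silence on hierarchy alone is no fault. The recommendation is to improve a method that the article does state.

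A reader might also infer that baseline differences within individual pairs bias the comparison. They do not if they average zero; they only add variance.

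Further, the comparison is not randomised. If the two groups would have changed in parallel without a regimen effect, the change score is the unbiased analysis and the bias formula above does not apply. That is a fair limit. However, by matching on intensity and back function the plan already chooses to condition on baseline, and covariate adjustment follows the same logic.

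Finally, good matching raises c and shrinks the gain. This is also true, and it is why the loss has to be read as a range. The figures at c = 0 are the upper end.

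**Conclusion.** The point holds in a limited form. The stated test for the matched contrast leaves out a baseline score that is available, and the text does not say whether this test or the planned regression gives the between-group result.

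The cost in precision is about 4% to 54% more pairs over the assumed ranges of rho and c. At rho = 0.5 it is 33%, 17% and 7% for c = 0, 0.5 and 0.8. It is negligible for large matched samples and worth recovering for rarer regimens.

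Bias arises only from a non-zero mean baseline imbalance that survives matching. Its size is about (1 - rho) times the imbalance, on condition that the baseline-adjusted model is correct. The plan's residual-imbalance step may deal with it, but the article does not connect that step to the reported contrast. All sizes rest on assumed correlations, SDs, differences and pair numbers, because the article gives none. The change is worth making because it costs almost nothing.

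**What to change.** In the Analytic approach section, state that each regimen difference in NRS and ODI, at each analysis time point, comes from the linear regression already planned, fitted in the matched sample with:

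- the follow-up score as outcome and regimen as the factor;
- the first-visit value of the same scale, as a continuous variable, and the other matching variables as covariates;
- standard errors that account for the matching, either clustered on pair or through a pair effect.

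Keep the paired t-test on change as a sensitivity result and label it as such. No new data or patients are needed, since the baseline scores are collected and a regression is already planned. The cost is a revised paragraph and slightly more modelling.

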### Sample size

Currently, there is no valid sample size calculation method for registry studies. According to experience, the principle of sample size estimation in multivariate analysis of variance is 5–10 times the number of variables. Our preliminary research variables are no more than 20, so the sample size of the study is 1000–2000, taking the maximum value, our sample size is set at not less than 2000. To ensure better data representation and reflect the diversity of acupuncture operations, we will recruit no less than 9 centers, at least 3 acupuncturists in each center, that is, at least 27 acupuncturists.

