Hierarchical models based on the pain grading, medical center, age group, gender, TCM syndromes and classification of diseases will be taken into account to explore the important factors affecting the effectiveness of acupuncture for CLBP [43–45]. Conditional logistic regression models adjusting by different variables to identify predictors of long-term effectiveness presented by ODI and NRS or recurrence at the12-week follow-up.

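### The matched regimen comparisons rest on a paired t-test and ordinary regression with no allowance for clustering by acupuncturist, so where regimen follows the practitioner, practitioner differences can pass for regimen effects

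*Protocol article*

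**What the plan says.** The Analytic approach section sets up the regimen contrasts as a matched design: "We will adopt the propensity score matching of patients at 1:1 to imitate an RCT". The contrasts named are traditional Chinese versus microacupuncture style, local versus non-local acupoints, and single versus combined therapy. The test is fixed: "Once matched, change in ODI and NRS between-group at different observation points will be calculated by paired t-test". Alongside it, "multivariate linear regression models will be employed to adjust the propensity score and baseline characteristics".

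The matching variables are given by example, and all of them describe the patient: "Baseline confounder will be equilibrated and matched on variables such as demographic data, medical history, duration, intensity, back function". Characteristics of doctors appear in this section only under descriptive analysis, and physician title only as an example of ranked data to be described. The logistic models concern baseline factors: "logistic regression models will be used to evaluate the magnitude of impacts contributed by baseline factors on acupuncture effectiveness".

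One further set of models could carry a cluster level: "Hierarchical models based on the pain grading, medical center, age group, gender, TCM syndromes and classification of diseases will be taken into account". Their stated purpose is to explore factors that affect effectiveness. They name centre but not acupuncturist, and they are not linked to the matched contrasts.

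The Sample size section plans not fewer than 2000 patients in at least 9 centres, with "at least 3 acupuncturists in each center, that is, at least 27 acupuncturists". Table 1 makes practitioner years of employment and professional title indispensable items.

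**The concern.** A paired t-test treats the matched pairs as independent of each other, and ordinary linear regression treats the patients as independent. Patients of one acupuncturist share that person's skill, manner and case mix, so their outcomes are likely to be correlated. If the two regimens are also spread unevenly across acupuncturists, two things go wrong. The difference between regimens absorbs the difference between the people who deliver them, and the standard error leaves out the between-practitioner variance. Matching on patient characteristics cures neither.

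The protocol's own premises make this more than a technicality. The Background says that operator experience can affect outcome. The second objective is to find key factors on both the implementation side and the physician side. The Abstract promises a preferred regimen. A finding in favour of a style that really reflects a few good or poor practitioners would defeat that purpose.

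**Working it through.** **Inputs from the protocol (Sample size).** At least 9 centres with at least 3 acupuncturists each: 9 × 3 = 27, which reproduces the stated figure. At least 2000 patients. Both are minima.

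**Assumptions.** The protocol gives no intraclass correlation (ICC) by acupuncturist and no information on how far regimen follows the practitioner. The range shown is ICC 0.01, 0.05 and 0.10. The share of a practitioner's patients who get that practitioner's favoured regimen runs from 100% (complete nesting) to 50% (equal mixing).

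**Step 1: cluster size.** m = 2000 / 27 = 74.07 patients per acupuncturist.

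**Step 2: complete nesting, by formula.** Design effect DE = 1 + (m − 1) × ICC. The naive standard error is too small by a factor √DE. The information is that of 2000 / DE independent patients. The true size of a nominal two-sided 5% test is 2 × P(Z > 1.96 / √DE).

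| ICC | DE | √DE | 2000 / DE | 1.96 / √DE | True size |
|---|---|---|---|---|---|
| 0.01 | 1 + 73.07 × 0.01 = 1.73 | 1.32 | 1156 | 1.49 | 14% |
| 0.05 | 1 + 73.07 × 0.05 = 4.65 | 2.16 | 430 | 0.91 | 36% |
| 0.10 | 1 + 73.07 × 0.10 = 8.31 | 2.88 | 241 | 0.68 | 50% |

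These figures hold only if each acupuncturist uses a single regimen. With 20% of patients lost (m = 59.3), the sizes become 12% / 32% / 45%.

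**Step 3: partial mixing, by simulation of the planned test.** The simulation had 27 acupuncturists with 74 patients each, random 1:1 pairs, a paired test, no true regimen effect, and 1500 runs per setting.

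| Share on favoured regimen | ICC 0.01 | ICC 0.05 | ICC 0.10 |
|---|---|---|---|
| 100% | 15% | 36% | 52% |
| 90% | 10% | 30% | 41% |
| 75% | 8% | 16% | 24% |
| 50% | 5% | 6% | 5% |

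The first row agrees with the formula. The last row is the nominal 5% within simulation error, so the inflation disappears when every practitioner uses both regimens equally.

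**Step 4: does a simple cluster correction suffice?** If only a few acupuncturists deliver one arm, it does not. With complete nesting and 27 clusters of 74, a standard clustered standard error with a normal critical value rejects a true null in about 18% of runs when 3 practitioners deliver the smaller arm, 14% with 4, and 11% with 5. In that setting the estimate itself also stays confounded with those individuals, whatever standard error is used.

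**The case against.** The strongest objection is that the protocol nowhere says that regimen is a practitioner habit. Table 2 records the acupuncture rationale for each patient at the first visit and combined therapy at every visit. The Discussion looks for programmes suited to different states and subtypes, which implies choice by patient. Single versus combined therapy is the contrast least likely to be fixed by practitioner. With equal mixing the planned test keeps its size. All of this stands. A reader might infer that practitioner effects will be reported as regimen effects with standard errors that are certainly too small. The documents do not support that: the effect depends on a degree of nesting and an ICC that they do not give.

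Second, a reader might infer that acupuncturist is excluded from the propensity score. The list of matching variables is introduced as examples and the covariates of the conditional logistic models are left open, so the text supports only that acupuncturist is not named. A full covariate list may properly sit in a fuller document. That limits the point about matching variables. It does not touch the paired t-test, which is a stated choice.

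Third, hierarchical models with centre are planned, and they may contain patient covariates; listing age group or gender there is no error in itself. But centre sits above acupuncturist (at least 3 per centre), and these models serve factor exploration rather than the matched contrasts.

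Fourth, this is an observational registry with largely exploratory aims, and its Limitations section concedes selection bias and hidden confounding. It does not mention clustering by practitioner, which is neither hidden nor unmeasured here.

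**Conclusion.** The point holds in conditional form. The stated test for the matched regimen contrasts makes no provision for clustering by acupuncturist, and no other planned model supplies it for those contrasts. Where regimen tends to follow the practitioner, regimen and practitioner effects can be confused and standard errors can be too small.

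The size runs from no inflation with equal mixing to a true size of about 50% for a nominal 5% test under complete nesting at an ICC of 0.10. If 75% of patients get the favoured regimen, it is about 8% to 24% over the ICC range shown. The ICCs and the degree of mixing are assumptions, and 2000 and 27 are planned minima. The risk is probably greatest for style and acupoint selection and least for single versus combined therapy, which is a judgement and not something the protocol states. A plan with as few as 27 practitioners should not rely on near-perfect mixing to keep its tests valid.

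**What to change.** 1. Replace the paired t-test as main analysis of the matched contrasts with a mixed model on the matched set: linear for NRS and ODI, logistic for effective rate, adjusted for the baseline score. Use random intercepts for acupuncturist within centre and small-sample degrees of freedom. Acupuncturist-clustered standard errors with a small-cluster correction are an alternative.
2. Match or compare within acupuncturist, or failing that within centre, where overlap allows. This is the step that addresses confounding; random intercepts or clustered standard errors alone do not remove it when few practitioners use a style.
3. Tabulate regimen use by acupuncturist for each contrast. Where few acupuncturists deliver one arm, state that the contrast cannot be separated from the practitioner.
4. Add practitioner years of employment and professional title as covariates.

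The cost is a change of analysis wording; Table 1 already collects the variables. The price is wider intervals, possibly fewer matched pairs, and perhaps a contrast that has to be reported as not separable from the practitioner.

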### Inclusion criteria

Chronic low back pain or acute onset of chronic low back pain were observed as the main objects to meet the diagnostic criteria for chronic low back pain.16 years≤Age ≤ 80 years;The main treatment method is acupuncture.Voluntarily participate in the patient registration study and sign informed consent.

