### Numerical rating scale (NRS)

Patients were asked to use the numbers 0–10 to quantify pain, with ‘0’ symbolize no pain and ‘10’ symbolize most pain. Higher the number, heavier the pain.

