### Limitations of study

In the initial stage, center selection bias maybe be inevitably affected by real recruitment results, we will promote geographical representation by expanding recruitment. Lacking the pre-defined comparable group will be the inevitable limitation, as well as selection bias. Although we will adopt the method of propensity score matching to implement post hoc randomization and conduct stratification analysis, hidden, unknown confounding factors will still exist. Perhaps, in future research, we can embed pragmatic randomized controlled trials, pRCTs with long-term follow-up into the platform as a sub-project, to obtain more reliable and abundant evidence [23, 56].

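### The exploratory hierarchical models use grouped pain and age although both are recorded in full, and list patient traits beside centre: a modest, avoidable loss of information

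*Protocol article*

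**What the plan says.** In the protocol article, Analytic approach, the factor models are described in one sentence. They are "Hierarchical models based on the pain grading, medical center, age group, gender, TCM syndromes and classification of diseases", and their purpose is "to explore the important factors affecting the effectiveness of acupuncture for CLBP". The sentence does not define hierarchical. It gives no cut points and no number of levels, and it does not say how the six items combine.

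Other sections show what is recorded:

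- Numerical rating scale: "Patients were asked to use the numbers 0–10 to quantify pain".
- Analytic approach, on descriptive statistics: "Quantitative data (Height, Weight, NRS, ODI, etc.) will be described by mean, standard deviation, median, maximum and minimum values". The plan itself treats the NRS as quantitative.
- Inclusion criteria: "16 years≤Age ≤ 80 years". Table 1 makes age an indispensable demographic item.
- Sample size, on clusters: "we will recruit no less than 9 centers, at least 3 acupuncturists in each center, that is, at least 27 acupuncturists".
- Sample size, on patients: "our sample size is set at not less than 2000".
- Limitations of study: propensity matching is meant to "implement post hoc randomization and conduct stratification analysis". Whether strata are taken jointly or one at a time is not stated.

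**The concern.** Two things in that sentence sit badly with the rest of the article.

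First, pain and age appear as a grading and a group, although finer values are available for every patient. Cutting a measured covariate treats all patients within a band as alike. Differences in severity or age inside a band are then unadjusted. Where they are related to another factor, such as syndrome, disease class or centre, part of their effect can be credited to that factor. These models look for factors that matter, so the blurring falls on their own purpose.

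Second, the list mixes two kinds of variable. Patients are clustered within centres. Gender, age, pain severity, syndrome and disease class are patient traits that can occur in any centre. The other cluster in the design, the acupuncturist within centre, is not in the list, although the objectives in the Background ask about factors from the physician's side. A reader cannot tell which items are levels and which are covariates.

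**Working it through.** The plan gives no figure on this point, so there is none to reproduce. The checks below show the size of the loss under stated assumptions. Pain grading is taken to mean bands of baseline NRS, the only stand-alone pain-intensity score in the article.

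**1. Information lost by grouping.** Assume a standard normal factor with a linear effect, cut into k equal-size groups at quantiles q_0, …, q_k. With φ the normal density, the mean of group j is m_j = k·[φ(q_{j−1}) − φ(q_j)]. The share of variance kept is R = (1/k)·Σ m_j². For k = 2 this is 2/π = 0.637.

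| Groups k | Kept, R | Lost, 1 − R |
|---|---|---|
| 2 | 0.637 | 36% |
| 3 | 0.793 | 21% |
| 4 | 0.861 | 14% |
| 5 | 0.897 | 10% |

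If confounding runs linearly through the factor, the covariance left after adjusting for groups is that within groups. About 1 − R of the linear confounding by that factor therefore remains.

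**2. An 11-point score in three bands.** Assume bands 0–3, 4–6 and 7–10 and a rounded normal baseline NRS. The share kept is 83% for mean 5 and SD 2, 81% for mean 5.5 and SD 1.8, and 76% for mean 6 and SD 1.5. This is close to the three-group row above.

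**3. Effect on precision.** With baseline–outcome correlation r, residual variance rises by the factor (1 − r²R)/(1 − r²).

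- r = 0.3, R = 0.86: (1 − 0.09 × 0.86)/0.91 = 1.014.
- r = 0.5, R = 0.79: (1 − 0.25 × 0.79)/0.75 = 1.07.
- r = 0.6, R = 0.64: (1 − 0.36 × 0.64)/0.64 = 1.20.

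The range is about 1% to 20%. The values of r are assumptions.

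**4. Do six factors produce empty cells?** The article implies 9 centres (its minimum) and 2 genders; the levels of the other four factors are assumed. The order is pain × centre × age × gender × syndrome × disease class, with N = 2000. The expected empty share is exp(−N/cells) for even filling. The uneven case makes each level 0.6 times as common as the one before.

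| Levels | Cells | Patients per cell | Empty, even | Empty, uneven | Main-effects parameters |
|---|---|---|---|---|---|
| 2×9×2×2×2×2 | 288 | 6.9 | 0.1% | 22% | 14 |
| 3×9×3×2×3×3 | 1458 | 1.4 | 25% | 56% | 18 |
| 3×9×4×2×4×5 | 4320 | 0.46 | 63% | 77% | 22 |

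The last column is 1 plus the sum of (levels − 1). Full crossing can thus be sparse. Entered as main effects, the same factors need 14 to 22 parameters for 2000 patients, and empty cells do no harm.

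**The case against.** The strongest reply is that this is one condensed sentence in a journal article. Functional form and the choice of fixed or random effects usually belong in an analysis plan, which is not shown. That answers a complaint about missing detail. It does not fully answer this point, because the sentence itself names grouped pain and grouped age.

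The reply carries more weight on three stronger readings that a reader might infer:

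- **Many cells will be empty.** The article does not say that the six factors are crossed or used as joint strata. The stratification in Limitations of study can be done one factor at a time.
- **Gender becomes a random level with one degree of freedom.** The article mentions no random effects, variance components or nesting. Hierarchical may also mean entering predictors in blocks, where patient traits belong.
- **The whole search for key factors is compromised.** The Analytic approach also plans logistic models for baseline factors, conditional logistic models for 12-week predictors, linear regression adjusting for baseline characteristics, and matching that includes intensity and back function. None of these is said to use grouped NRS or age.

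It is also fair that the percentages depend on normality, linearity and equal groups, and that the loss of precision may be as small as about 1%. Finally, pain grades and age groups have a legitimate use under the objective on subtypes suited to acupuncture, so they should not be banned from results.

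**Conclusion.** The point holds in a limited form. The stated models use grouped pain and age where full values exist, and they list patient traits beside centre without separating clusters from covariates. The direction of the loss is clear when the factor acts roughly linearly. Its size is about 36% to 10% of a grouped factor's linear information for 2 to 5 equal groups, with a like share of linear confounding by that factor left in these models. Both figures assume a normal factor and a linear effect; the true size depends on cut points not given. Sparse cells are only a conditional risk: 288 to over 4000 cells for 2000 patients under the assumed level counts, and only if the factors are crossed. Severity is low. One of several exploratory analyses is affected, and the matched comparisons are a separate analysis.

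**What to change.** Reword the hierarchical-model sentence in Analytic approach so that:

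- baseline NRS and age enter as continuous covariates, linear or with a 3-knot spline;
- gender, TCM syndrome and disease class enter as patient-level fixed effects;
- hierarchical (random) levels are kept for true clusters, namely centre and acupuncturist within centre;
- pain grades and age groups are used for descriptive tables and for presenting subgroup estimates under the subtype objective.

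No new data are needed. The cost is a few degrees of freedom at most: a linear term uses 1 and a 3-knot restricted cubic spline 2, against k − 1 for k groups. Presentation becomes slightly less simple. With as few as 9 centres, the centre variance will be estimated loosely, and this should be said when results are reported. The change is best made before the outcome data are analysed.
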